##### Propensity for β-adrenoreceptor blocking drug prescription

This will be calculated as in cohort study 1. Additionally, propensity score will include hand osteoarthritis (interphalangeal or thumb base osteoarthritis—a marker of generalised osteoarthritis), neck pain or back pain, spinal degenerative diseases (indicating osteoarthritis in the spine—a marker of generalised osteoarthritis), arthroscopic knee or hip surgery, number of analgesic prescriptions between the first consultation for knee/hip osteoarthritis and β-adrenoreceptor blocking drug prescription, aspirin, statin and bisphosphonate, and glucosamine/chondroitin sulfate prescription in the 12-month period prior to cohort entry, as these may affect knee or hip osteoarthritis progression.^29–33^

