## Introduction

Osteoarthritis is the most common form of arthritis worldwide. Its prevalence is increasing due to an ageing population and obesity epidemic.^1 2^ It is a leading cause of disability among older adults, with an estimated lifetime risk of 25% and 45% for hip and knee osteoarthritis, respectively.^3 4^ There is no specific therapy for osteoarthritis, and management focuses on symptomatic treatment, with total joint replacement reserved for those with severe symptomatic disease. However, analgesic and anti-inflammatory drugs only have modest efficacy for osteoarthritis pain, with mean Western Ontario and McMaster Universities Arthritis Index improvement of 3.99–11.24 across a spectrum of non-steroidal anti-inflammatory drugs (NSAIDs) and opioids.^5^ Apart from this, NSAIDs and cyclo-oxygenase II inhibitors increase the risk of gastrointestinal bleeding, acute kidney injury, chronic kidney disease, coronary heart disease, hypertension, stroke and congestive cardiac failure, and are associated with increased cardiovascular mortality.^6–18^ These adverse effects are particularly important for people with osteoarthritis as they already have a high burden of cardiovascular comorbidities and risk factors.^19 20^ Consequently, healthcare practitioners are reluctant to prescribe NSAIDs as these patients are often on antiplatelet therapy for primary prevention or dual antiplatelet therapy following a cardiovascular event, meaning that prescription of NSAIDs would expose patients to unacceptably high bleeding risk, and so the prescription of potent opioids for osteoarthritis pain has increased over the last decade.^21^ However, opioids induce dependence and increase the risk of falls, fractures and death.^22–25^ Thus, there is a need to develop safe, effective, well-tolerated, non-addictive analgesics to target osteoarthritis pain that can be prescribed safely to patients with cardiovascular comorbidities.

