###### Unexposed

Age (5-year age band based on year of birth), sex, GP surgery, year first registered in CPRD (±1 year) and propensity score for β-adrenoreceptor blocking drug prescription matched to the exposed participants.

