##### Propensity for β-adrenoreceptor blocking drug prescription

As participants prescribed β-adrenoreceptor blocking drugs are likely to have comorbidities, be older and have a high body mass index (BMI), a propensity score for β-adrenoreceptor blocking drug prescription will be calculated using a cumulative logit regression model and including demographic factors and relevant diagnoses at any time prior to β-adrenoreceptor blocking drug prescription (box 1).

Box 1List of potential variables to be included in the calculation of propensity score for β-adrenoreceptor prescriptionDemographic factors.Body mass index (WHO classification categories)*, smoking status* and deprivation score (general practice-level Index of Multiple Deprivation Score).Comorbidities.Hypertension, angina, myocardial infarction, congestive cardiac failure, atrial fibrillation, stroke, high cholesterol, chronic kidney disease, diabetes, anxiety, migraine, Charlson Comorbidity Index (excluding comorbidities in the propensity score) and duration in years of cardiovascular comorbidities prior to cohort entry.Drug prescriptions.Calcium channel blockers, ACE inhibitors, angiotensin II receptor antagonists, bendroflumethiazide, aldosterone antagonists, loop diuretics, alfa-adrenoreceptor blocking drugs, nitrates, nicorandil, aspirin, clopidogrel, statin, fibrate, vitamin K antagonists and non-steroidal anti-inflammatory drugs (in the progression cohort), and as a marker of severity of underlying disease at cohort entry the number of antihypertensive, antiarrhythmic or antianginal drugs prescribed in the 12-month period prior to cohort entry.*Categorised as missing if not available.

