##### Exclusion criteria

Exclusion criteria will be consultation for any of the following prior to the index date:

Osteoarthritis at any joint.Knee, hip, neck or back pain.Conditions causing joint damage or chronic pain: autoimmune inflammatory rheumatic diseases, such as rheumatoid arthritis, psoriatic arthritis, ankylosing spondylitis, lupus, polymyalgia rheumatica, gout, radiculopathy, neuropathy and fibromyalgia.Contraindications to prescription of β-adrenoreceptor blocking medicines: chronic obstructive pulmonary disease, asthma, peripheral vascular disease, heart block, aortic stenosis and hypertrophic obstructive cardiomyopathy.Two consecutive prescriptions for any opioid, any NSAID, gabapentin, pregabalin, duloxetine or amitriptyline prior to the index date.<1 year up-to-standard registration prior to index date to reduce the risk of prevalent cases (eg, with osteoarthritis) being classified as incident cases.^28^

The cohort entry date will be the index date. The unexposed participants will be allocated the index date of their matched exposed participant.

The cohort exit date will be the earliest of the date of the last prescription of β-adrenoreceptor blocking drug prescription, plus 4 weeks or a matched pseudo-exit date for the matched controls, date of the first outcome, date of death, transfer-out date, date of the last data collection or study end date (31 December 2017).

#### Cohort study 2

Cohort study 2 will be on β-adrenoreceptor blocking drug prescription and total joint replacement and analgesic use. The exposure will be as in cohort study 1.

The outcome will be total knee replacement (primary), total hip replacement and analgesic prescription: (1) NSAIDs, (2) opioids, (3) gabapentin or pregabalin, and (4) amitriptyline.

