##### Inclusion criteria

###### Exposed

As in cohort study 1 above.Consultation for knee or hip osteoarthritis prior to the first of the two prescriptions for β-adrenoreceptor blocking drugs.

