###### Unexposed

As in cohort study 1, but with additional matching for prior consultation for knee or hip osteoarthritis to exposed participants.

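### The Study 2 propensity score counts analgesics over a window of any length and lists neither osteoarthritis duration nor a recent analgesic count, so severity adjustment of the knee replacement HR may be incomplete

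*Protocol article*

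**What the plan says.** All references are to the protocol article.

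- **Severity covariate.** Cohort study 2, Propensity for β-adrenoreceptor blocking drug prescription, adds to the score the "number of analgesic prescriptions between the first consultation for knee/hip osteoarthritis and β-adrenoreceptor blocking drug prescription". The 12-month period at the end of that sentence belongs to other drugs; the analgesic count has its own start and end.
- **Window start.** Eligibility needs a "Consultation for knee or hip osteoarthritis prior to the first of the two prescriptions for β-adrenoreceptor blocking drugs", with no minimum or maximum interval.
- **Window end in the unexposed.** "The unexposed participants will be allocated the index date of their matched exposed participant" (Cohort study 1, Exclusion criteria, carried over to Study 2).
- **Matching.** Study 2 has "additional matching for prior consultation for knee or hip osteoarthritis to exposed participants". The date of that consultation is not a named matching factor. Age band, sex, practice and registration year (within one year) are matched as in Study 1.
- **Cardiovascular counterpart.** For cardiovascular disease, Box 1 lists both "duration in years of cardiovascular comorbidities prior to cohort entry" and "the number of antihypertensive, antiarrhythmic or antianginal drugs prescribed in the 12-month period prior to cohort entry", the latter explicitly as a severity marker at cohort entry. Osteoarthritis gets neither form.
- **Other relevant terms.** Box 1 adds NSAIDs for the progression cohort, with no window. The Study 2 score adds arthroscopic surgery, hand osteoarthritis, spinal disease and neck or back pain.

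**The concern.** The count has no time base. Twelve prescriptions in one year since the osteoarthritis consultation and twelve over ten years get the same value, although the yearly rates are 12 and 1.2. Someone first coded a week before the index date scores close to zero however much pain relief they were already receiving. The Sensitivity analyses section itself says that osteoarthritis codes may come only after several consultations for knee or hip pain.

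Current pain plausibly drives knee replacement, the primary outcome of Study 2. The Introduction supplies a route from analgesic use to exposure: it says that NSAIDs "increase the risk of gastrointestinal bleeding, acute kidney injury, chronic kidney disease, coronary heart disease, hypertension, stroke and congestive cardiac failure", and several of these are conditions for which the plan expects β-blockers to be prescribed. If matched groups share a count but differ in current pain, the replacement HR carries residual confounding. The planned balance check would not reveal this, because the count can balance while osteoarthritis duration and recent use do not.

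The point bears mainly on joint replacement. For the new-analgesic outcomes, people with two consecutive analgesic prescriptions before the index date are already excluded.

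**Working it through.** **Does any stated figure depend on this covariate?** No. The Study 2 sample size reproduces without it. Required events = (2.576 + 0.842)² / (0.2 × 0.8 × (ln 0.70)²) = 573.77, and 573.77 / 0.009 = 63 752, against 63 753 stated.

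**Illustrative simulation 1: count against count plus duration.** The documents give no osteoarthritis durations, prescribing rates or severity associations, so every input is an assumption.

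- Severity S is standard normal and constant over time.
- Time since first osteoarthritis consultation, T, is log-normal with median 4 years and log-SD s.
- Count C ~ Poisson(3 · exp(bS + 0.5e) · T), with e standard normal.
- logit P(exposed) = −1.4 + 0.3S + g · ln(T/4).
- Replacement hazard ∝ exp(0.7S), true HR 1.
- 400 000 people per scenario, fine stratification, Mantel-Haenszel ratio.
- Share of bias left = ln(adjusted HR) / ln(crude HR). Crude HR was about 1.22 to 1.24.

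Example (b = 0.8, s = 0.8, g = 0): crude 1.224, stratified on count 1.132, on count plus T 1.074. Shares left are ln 1.132 / ln 1.224 = 61% and ln 1.074 / ln 1.224 = 35%.

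| b | s | R² of log count with time / severity | Left after count (%), g = 0 / +0.3 / −0.3 | Left after count + T (%), same order |
|---|---|---|---|---|
| 0.4 | 0.3 | 0.15 / 0.26 | 74 / 68 / 78 | 68 / 69 / 68 |
| 0.4 | 0.8 | 0.54 / 0.14 | 86 / 65 / 107 | 69 / 69 / 70 |
| 0.4 | 1.2 | 0.69 / 0.09 | 91 / 65 / 119 | 70 / 70 / 72 |
| 0.8 | 0.3 | 0.08 / 0.58 | 40 / 34 / 48 | 35 / 35 / 36 |
| 0.8 | 0.8 | 0.38 / 0.39 | 61 / 29 / 91 | 35 / 35 / 37 |
| 0.8 | 1.2 | 0.54 / 0.28 | 72 / 29 / 116 | 38 / 38 / 39 |
| 1.2 | 0.3 | 0.05 / 0.75 | 24 / 18 / 30 | 20 / 20 / 21 |
| 1.2 | 0.8 | 0.25 / 0.58 | 42 / 9 / 72 | 21 / 20 / 21 |
| 1.2 | 1.2 | 0.39 / 0.46 | 54 / 5 / 101 | 23 / 22 / 23 |

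- The raw count left 5% to 119%, and more than half in 16 of 27 scenarios.
- Adding T helped in all 18 scenarios with g = 0 or −0.3. It left 1 to 17 percentage points more in the nine with g = +0.3, where the time component of the count happens to offset part of the severity bias.
- With a weak severity signal in prescribing (b = 0.4), about 70% stays even after T is added, so the window is then not the main cause.

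**Illustrative simulation 2: letting pain change over time.** Assumed inputs, 600 000 people, true HR 1, crude HR 1.16. The three values are for past-to-current pain correlation 1.0, 0.7 and 0.4.

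| Adjustment | Exposure unrelated to osteoarthritis duration | Duration raises exposure (log-odds 0.2 per SD) and replacement (log-HR 0.3 per SD) |
|---|---|---|
| Cumulative count | 1.105, 1.124, 1.141 | 1.03, 1.07, 1.11 |
| 12-month count alone | 1.061, 1.060, 1.057 | 1.11, 1.11, 1.11 |
| Cumulative count + duration | 1.039, 1.075, 1.100 | not run |

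A 12-month count alone is clearly better in the first setting and no better or worse in the second.

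**Adding the 12-month count to the cumulative count.** In 12 scenarios of this kind the HR was about 1.03 to 1.05, against 1.04 to 1.14 for the cumulative count alone, and bias fell in all 12. In a wider grid of 81 (the ranges of simulation 1 plus past-to-current correlation 0.5 to 1.0), bias fell in 78. The three exceptions were worse by at most about 5 percentage points. All three needed perfect past-to-current correlation and exposure rising with duration.

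**The case against.** The strongest defence is that the count does not stand alone. Box 1 enters NSAIDs separately for this cohort, with no stated tie to the osteoarthritis consultation. Arthroscopy is in the score. GP consultations and referrals in the preceding 12 months may enter the model. Replacement within three months of the index date is excluded. A sensitivity analysis on knee or hip pain at cohort entry addresses late coding. Matching on age band and registration year, with a shared index date, limits how far durations can diverge. Residual confounding is acknowledged. The simulations include none of these safeguards, and their upward bias runs against the hypothesised benefit. Box 1 also lists only potential variables, and a condensed article may leave coding to the full protocol.

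Much of this stands as mitigation. It does not remove the point. The NSAID term has no stated window or count, and arthroscopy is a past event. The hand, spine and neck or back terms add little, because osteoarthritis at other joints and neck or back pain are exclusions. Registration year bounds record length, not osteoarthritis duration. The count's window is spelled out, so it is a choice made in the text and not a detail left open.

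A reader might infer that the count reflects elapsed time as much as pain, or that most severity confounding stays in the HR. The documents support neither. Under assumed inputs, time explained 5% to 69% and severity 9% to 75% of the variance in log count, and the bias left ranged from almost none to more than all of it. A reader might also infer that the count should be swapped for a 12-month count; the second setting of simulation 2 shows why that can backfire.

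**Conclusion.** The point holds as a moderate, cheaply repaired weakness. The only analgesic count in the Study 2 score is not standardised for time, and neither osteoarthritis duration nor a recent analgesic count is listed in the score or the matching. Adjustment for osteoarthritis severity in the total knee replacement HR may therefore be incomplete.

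Neither size nor direction can be derived from the documents. The upward bias in the simulations follows from assuming that greater severity makes exposure more likely, and the percentages depend on assumed durations, prescribing rates and associations. No failure of the HR is shown, and the sample size is unaffected. What is robust is that adding recent use to the cumulative count helped in nearly every scenario tried. Adding duration helped unless exposure rose with duration while replacement did not depend on it. The two additions were each examined alongside the cumulative count, not jointly.

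**What to change.** In Cohort study 2, Propensity for β-adrenoreceptor blocking drug prescription, keep the cumulative analgesic count and add:

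- (a) the number of analgesic prescriptions in the 12 months before the index date, whether or not they precede the first osteoarthritis code;
- (b) the time since the first knee or hip osteoarthritis consultation.

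Report balance on both after matching, and treat any imbalance under the existing rule for unbalanced covariates. Do not drop the cumulative count in favour of the 12-month count.

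The cost is one or two extra terms in the score and slightly more programming. The prescription records are already needed for the existing count. The exclusion of people with less than one year of up-to-standard registration means that the 12-month window is observed for everyone.

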##### Exclusion criteria

Exclusion criteria will be previous consultation for any of the following prior to the first prescription of β-adrenoreceptor blocking drug:

Osteoarthritis at any other joint.Neck or back pain.Conditions associated with joint damage or chronic pain (as above).Conditions contraindicating prescription of β-adrenoreceptor blocking medicines (as above).Previous knee or hip replacement.Knee or hip joint replacement within 3 months of the date of the first β-adrenoreceptor blocking drug prescription or matched index date in the unexposed participants. These will be excluded because we do not expect β-adrenoreceptor blocking drug prescription to reduce total joint replacement rates immediately and may be commenced during preanaesthetic check-up.<1 year up-to-standard registration prior to the first qualifying prescription of β-adrenoreceptor blocking drug.^28^
Additionally, participants who receive two consecutive prescriptions for opioids, NSAIDs, gabapentin, pregabalin, duloxetine or amitriptyline prior to the index date will be excluded from the cohort when examining the association between β-adrenoreceptor blocking drug prescription and new analgesic prescription.

The cohort entry and exit dates will be as in cohort study 1. Nearest neighbour matching (±0.2 SD) will be used to match exposed to unexposed participants.

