### Statistical analysis

Covariate balance between matched exposed and unexposed participants will be examined. Unbalanced covariates will be included in the model as separate covariates. Other covariates that do not influence exposure but influence outcomes or reflect health-seeking behaviour alone may be included in the model after evaluating their balance between exposed and unexposed groups. These are the following:

Number of GP consultations in the 12-month period preceding cohort entry.Number of hospital outpatient referrals in the 12-month period preceding cohort entry.Number of hospital admissions in the 12-month period preceding cohort entry.Total number of GP consultations for knee or hip injury prior to cohort entry.Non-osteoporotic fractures, defined as fractures in any bone except the femur, distal radius and vertebrae, after the age of 18 years but before the age of 50 years in women and 60 years in men. This is a surrogate for physically active occupation or lifestyle that may associate with incident osteoarthritis.

Participants will enter the cohort on the index date, and data will be censored at the earliest of an event, study end date (31 December 2017), date of death, transfer out of CPRD for all outcomes, and additionally date of the last prescription of β-adrenoreceptor blocking drugs, plus 4 weeks (usual duration of GP prescription in the UK) for incident osteoarthritis, incident knee or hip pain, or new analgesic prescription. Given the reported effects of propranolol on pain sensitivity in patients with fibromyalgia,^34^ we anticipate β-adrenoreceptor blocking drugs to have an analgesic effect in the short term, and outcome events >4 weeks after the date of the last β-adrenoreceptor blocking drug prescription will not be included in the analysis, except for total joint replacement which may be delayed due to a period of analgesia.

Time to event data in the exposed and unexposed groups will be compared using Kaplan-Meier survival curves. Schoenfeld residuals will be examined to see if survival curves meet the assumptions of the proportional hazard model. Cox proportional HRs and 95% CI will be calculated for each incident outcome using the first Read code for the event. Similarly, HRs will be calculated for new analgesic prescriptions, defined as prescription for NSAIDs, opioids, gabapentin and pregabalin, respectively, in those exposed to β-adrenoreceptor blocking drugs, with unexposed as the referent.

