## Discussion

Findings from several studies suggest that β-adrenoreceptor blocking drugs may have an analgesic effect in osteoarthritis. β-adrenoreceptors are distributed widely in the central nervous system, and polymorphisms in β2-adrenoreceptor genes associate with fibromyalgia, chronic widespread pain and irritable bowel syndrome.^39–42^ They have demonstrated analgesic potential in randomised controlled trials in other painful conditions such as fibromyalgia, temporomandibular dysfunction and migraine, and in animal models of arthritis and pain.^34 43–45^ Moreover, β-adrenoreceptor blocking drugs also reduce the need for intraoperative anaesthetics and postoperative analgesia.^46^ This effect has been observed with the highly β1-adrenoreceptor selective drug esmolol, non-β1β2 selective drugs such as propranolol, and drugs such as bupranolol which block the β3-adrenoreceptor.^46^ The mechanism by which β-adrenoreceptor blocking drugs provide analgesia includes heterodimerisation of β2-adrenoreceptors with µ-opioid receptors increasing the latter’s sensitivity,^47^ inhibitory effects on tetrodotoxin-resistant sodium channels in the dorsal root ganglion neurons,^48^ and increased inhibitory neurotransmitter release in the spinal ganglions through a mechanism involving β1-adrenoreceptor-independent Ca^2+^ entry.^45^ If our study demonstrates analgesic potential for β-blockers, we will conduct clinical trials to confirm these findings. If our programme of research demonstrates meaningful analgesic effects of β-blockers for osteoarthritis pain, this class of drugs may be preferred in the treatment of cardiovascular diseases for people with comorbid symptomatic osteoarthritis.

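### Study 2 counts new analgesics whatever their indication and keeps people with prior migraine, so part of the analgesic HR may reflect migraine and not osteoarthritis pain

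*Protocol article*

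**What the plan says.** **Exclusions.** The exclusion list of Cohort study 2 removes people with "Conditions associated with joint damage or chronic pain (as above"). The list it points to, under Cohort study 1, covers inflammatory rheumatic diseases and ends with "polymyalgia rheumatica, gout, radiculopathy, neuropathy and fibromyalgia". Migraine is not on it.

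**Propensity score.** Box 1 lists migraine among the comorbidities: "chronic kidney disease, diabetes, anxiety, migraine, Charlson Comorbidity Index". For Cohort study 2 the score carries over: "This will be calculated as in cohort study 1", with further variables added. Prior migraine is therefore something to balance and not a reason to leave the cohort.

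**Outcome.** The opening of Cohort study 2 defines the outcome as "analgesic prescription: (1) NSAIDs, (2) opioids, (3) gabapentin or pregabalin, and (4) amitriptyline". The Statistical analysis section has "new analgesic prescriptions, defined as prescription for NSAIDs, opioids, gabapentin and pregabalin, respectively". Neither ties the prescription to osteoarthritis. They also differ on amitriptyline, which only the first names.

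**Interpretation.** The Introduction hypothesises fewer analgesic prescriptions in people with osteoarthritis and puts this down to an analgesic effect. The Discussion supports the idea with randomised trials in "other painful conditions such as fibromyalgia, temporomandibular dysfunction and migraine".

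**The concern.** The new-analgesic HR is meant to show whether β-blockers relieve osteoarthritis pain. An NSAID or opioid prescribed for migraine counts as an event just as one prescribed for a knee does. If β-blockers reduce migraine, exposed people with migraine will need fewer analgesics than matched unexposed people with migraine, even if the drug does nothing for osteoarthritis.

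Matching on migraine does not address this. The propensity score makes migraine about equally common in the two groups, which deals with migraine as a confounder. The difficulty here is a possible effect of the exposure within people who have migraine, and that remains under perfect balance. Adding migraine as a covariate has the same limit.

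The Discussion says that a finding of analgesic potential would lead to clinical trials, and that meaningful effects across the research programme could lead to β-blockers being preferred in people with cardiovascular disease and osteoarthritis. It therefore matters whether a reduction in analgesic prescribing comes from osteoarthritis.

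**Working it through.** **1. The plan's own figures.** The Sample size section gives none for the analgesic outcomes. Its HR of 0.70 belongs to incident osteoarthritis and total knee replacement. For knee replacement, Schoenfeld's formula with two-sided α = 0.01, 80% power and an exposed share of 0.2 gives (2.576 + 0.842)² / [0.2 × 0.8 × (ln 0.70)²] = 573.77 events. Divided by 0.009 per person-year (one year per person), this is 63 752.4, which rounds up to the stated 63 753. The figure reproduces but has no bearing on the analgesic outcomes.

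**2. Do other planned steps remove the problem?**
- *Prior-analgesic exclusion (Cohort study 2).* People with two consecutive earlier analgesic prescriptions leave this analysis. That removes regular users, but not people with migraine who have not yet had such prescriptions.
- *Restricted analyses (Sensitivity analyses).* The five groups are hypertension, atrial flutter or fibrillation, angina, angina with one of the former, and cardiac failure. All are defined by having a cardiovascular diagnosis. None excludes people who also have migraine.
- *Stratification by indication (Abstract).* This is planned in general terms, but the indications spelled out in the body are the cardiovascular ones.
- *Interaction tests (Statistical analysis).* These cover statin, aspirin and bisphosphonate.

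None of these changes the main analgesic HR.

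**3. Illustrative size.** Set the osteoarthritis effect to null and let migraine be perfectly balanced. All three inputs are assumptions; the documents give none of them:
- m: share with migraine, equal in both groups
- k: analgesic prescribing rate in unexposed people with migraine, relative to unexposed people without
- r: rate ratio for β-blocker against none, within migraine

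Rate ratio = [(1 − m) + m·k·r] / [(1 − m) + m·k]

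| m | k | r = 0.9 | r = 0.7 | r = 0.5 |
|---|---|---|---|---|
| 2% | 1 | 0.998 | 0.994 | 0.990 |
| 2% | 3 | 0.994 | 0.983 | 0.971 |
| 5% | 1 | 0.995 | 0.985 | 0.975 |
| 5% | 3 | 0.986 | 0.959 | 0.932 |
| 10% | 1 | 0.990 | 0.970 | 0.950 |
| 10% | 3 | 0.975 | 0.925 | 0.875 |

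The two corners written out:
- m = 0.02, k = 1, r = 0.9: (0.98 + 0.018) / (0.98 + 0.02) = 0.998
- m = 0.10, k = 3, r = 0.5: (0.90 + 0.15) / (0.90 + 0.30) = 1.05 / 1.20 = 0.875

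**4. Direction.** The ratio is below 1 whenever r < 1 and above 1 whenever r > 1. The observed r need not be below 1. Box 1 diagnoses may date from any time before the prescription, so exposed people may have migraine active enough to need a preventive while their comparators carry only an old code. That difference in severity would raise analgesic use among the exposed.

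**The case against.** **Partial safeguards exist.** The prior-analgesic exclusion removes the heaviest users. The cardiovascular restrictions would probably drop many people prescribed β-blockers for migraine, and the Abstract plans stratification by indication. This stands as mitigation. It does not change the main HR, and no specified analysis takes out comorbid migraine.

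**The exclusion list follows its own rule.** It selects conditions that cause joint damage or chronic pain, not conditions that respond to β-blockers. A reader might infer that excluding fibromyalgia while keeping migraine is an internal contradiction, since the Discussion names them together. The documents do not support that, because the list never used response to β-blockers as a criterion.

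**The evidence statement is modest.** A reader might infer that the protocol says β-blockers work in migraine. The Discussion claims only trial evidence of analgesic potential.

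**The distortion could be small.** At a 2% migraine share it is at most about 3% on the HR scale over this range. A reader might instead infer that migraine alone could produce an HR of 0.70. That takes a 20% share, a fourfold rate and removal of 80% of the excess: (1 + 0.2 × 3 × 0.2) / (1 + 0.2 × 3) = 1.12 / 1.60 = 0.70. These inputs are extreme and sit badly with a cohort stripped of prior regular analgesic users. Even a 15% share with k = 3 and r = 0.5 gives 1.075 / 1.30 = 0.827. Nor is 0.70 a planning value for the analgesic outcomes.

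**Extensions lack support.** A reader might extend the argument to anxiety and pregabalin, or to differences between β-blocker classes. The protocol does not link pregabalin to anxiety or say which class is used for migraine, so neither point is made here.

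**Conclusion.** The concern holds in a limited form. The outcome counts analgesics for any indication, people with prior migraine remain, and the protocol itself gives grounds to expect a β-blocker effect in migraine. Balancing prevalence cannot separate that effect from one on osteoarthritis pain.

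Under the stated assumptions, and with no true osteoarthritis effect, the HR would lie between about 0.998 and 0.875. That range rests on equal migraine severity in the two groups. If migraine is more active in the exposed, the distortion could run the other way. The actual size, and so the net direction, cannot be found from the documents.

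Only the new-analgesic outcomes of Study 2 are affected, and these are secondary. Total knee replacement, the primary outcome of that study, is outside this point. It is a worthwhile and inexpensive improvement, not a flaw that undermines the study.

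**What to change.** For the Study 2 new-analgesic outcomes only, pre-specify an analysis that excludes everyone, exposed and unexposed, with a migraine consultation before the index date. State whether a consultation on the index date itself counts, because a first prescription for migraine may fall on that day. Report the result beside the main HR for each drug class, and attribute a reduction to osteoarthritis analgesia only if it persists in this analysis. Judge persistence by the estimate and its interval, not by significance alone, since the restricted cohort is smaller.

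The migraine codes are already needed for Box 1, so no new data are required. The cost is a modest loss of participants and precision in these secondary outcomes. Migraine first recorded after the index date would remain. The main analysis and the joint replacement analyses stay as they are.
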